**SA = Strongly Agree A= Agree NS= Not Sure D = Disagree SD= Strongly Disagree**

| 1. I often have the feeling that I cannot handle things very well | SA | A | NS | D | SD |
| --- | --- | --- | --- | --- | --- |
| 2. I find myself giving up more of my life to meet my children’s needs than I ever expected | SA | A | NS | D | SD |
| 3. I feel trapped by my responsibilities as a parent. | SA | A | NS | D | SD |
| 4. Since having this child, I have been unable to do new and different things | SA | A | NS | D | SD |
| 5. Since having a child, I feel that I am almost never able to do things that I like to do | SA | A | NS | D | SD |
| 6. I am unhappy with the last purchase of clothing I made for myself | SA | A | NS | D | SD |
| 7. There are quite a few things that bother me about my life | SA | A | NS | D | SD |
| 8. Having a child has cause more problems than I expected in my relationship with my spouse (or male/female friend) | SA | A | NS | D | SD |
| 9. I feel alone and without any friends | SA | A | NS | D | SD |
| 10. When I go to a party, I usually expect not to enjoy myself | SA | A | NS | D | SD |
| 11. I am not as interested in people as I used to be | SA | A | NS | D | SD |
| 12. I don’t enjoy things as I used to | SA | A | NS | D | SD |
| 13. My child rarely does things for me that make me feel good | SA | A | NS | D | SD |
| 14. Sometimes I feel my child doesn’t like me and doesn’t want to be close to me | SA | A | NS | D | SD |
| 15. My child smiles at me much less than I expected | SA | A | NS | D | SD |
| 16. When I do things for my child, I get the feeling that my efforts are not appreciated very much | SA | A | NS | D | SD |
| 17. When playing, my child doesn’t often giggle or laugh | SA | A | NS | D | SD |
| 18. My child doesn’t seem to learn as quickly as most children | SA | A | NS | D | SD |
| 19. My child doesn’t seem to smile as much as most children | SA | A | NS | D | SD |
| 20. My child is not able to do as much as I expected | SA | A | NS | D | SD |
| 21. It takes a long time and it is very hard for my child to get used to new things. | SA | A | NS | D | SD |

| For the next statement, choose your response from the choices “1” to “5” below  22. I feel that I am:  1. Not very good at being a parent  2. A person who has some trouble being a parent  3. An average parent  4. A better than average parent  5. A very good parent |  |  |  |  |  |
| --- | --- | --- | --- | --- | --- |
| 23. I expected to have closer and warmer feelings for my child than I do and this bothers me | SA | A | NS | D | SD |
| 24. Sometimes my child does things that bother me just to be mean | SA | A | NS | D | SD |
| 25. My child seems to cry or fuss more often than most children | SA | A | NS | D | SD |
| 26. My child generally wakes up in a bad mood | SA | A | NS | D | SD |
| 27. I feel that my child is very moody and easily upset | SA | A | NS | D | SD |
| 28. My child does a few things which bother me a great deal | SA | A | NS | D | SD |
| 29. My child reacts very strongly when something happens that my child doesn’t like | SA | A | NS | D | SD |
| 30. My child get’s upset easily over the smallest thing | SA | A | NS | D | SD |
| 31. My child’s sleeping or eating schedule was much harder to establish than I expected | SA | A | NS | D | SD |
| For the next statement, choose your response from the choices “1” to “5” below  32. I have found that getting my child to do something or stop doing something is:   1. Much harder than I expected  2. Somewhat harder than I expected  3. About as hard as I expected  4. Somewhat easier than I expected  5. Much easier than I expected |  |  |  |  |  |
| For the next statement, choose your response form the choices “10+” to “1-3”  33. Think carefully and count the number of things which your child does that bother you  For example: dawdles, refuses to listen, overactive, cries interrupts, fights, whines etc. | 10+ | 8-9 | 6-7 | 4-5 | 1-3 |
| 34. There are some things my child does that really bother me a lot | SA | A | NS | D | SD |
| 35. My child makes more demands on me than most children | SA | A | NS | D | SD |
| 36. My child makes more demands on me than most children | SA | A | NS | D | SD |

APPENDIX J. WORLD HEALTH ORGANIZATION QUALITY OF LIFE ASSESSMENT BREF (WHOQOL-BREF)^[[6]](#footnote-6)^

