***Introduction***. Postpartum depression (PPD) and sub-clinical PPD affect approximately 8 to 15% of Canadian women following childbirth (Chalmers et al., 2008). The disorder is debilitating and impacts a woman’s quality of life and her ability to care for and connect with her infant. PPD is also related to short- and long-term consequences for the infant (Tronick & Reck, 2009). Unfortunately, PPD is undertreated for reasons including lack of access to providers and limited mobility. Using the internet to deliver therapy is an innovative way to improve access to psychological treatment. Evidence has suggested that internet cognitive behavior therapy (ICBT) results in significantly larger effect sizes compared to all other online interventions (Barak et al., 2008) and that therapist-assisted ICBT (TAICBT) is comparable to in-person CBT (Spek, 2007).While there is evidence to support the efficacy of TAICBT for the treatment of major depression (Cuijpers et al., 2010), to date, researchers have yet to determine whether this modality is efficacious for the treatment of PPD.

***Purpose and Hypotheses****.* The proposed study will determine whether TAICBT is more efficacious than a waitlist control (WLC) condition in reducing depressive symptom severity, anxiety, general stress, parental stress, and for improving quality of life for women with PPD. It is hypothesized that TAICBT participants will demonstrate significantly greater symptom and clinical improvement from pre- to post-treatment on all outcome measures. It is also expected that symptom improvements will be maintained four weeks following the conclusion of treatment. Given that the TAICBT has not been examined in PPD populations, treatment expectancy, satisfaction, and therapeutic alliance will also be investigated. It is hypothesized that: (a)TAICBT participants will report satisfaction with the treatment,(b) significant associations will be revealed between post-treatment therapeutic alliance ratings and symptom changes scores, and (c) treatment expectancy and satisfaction will be moderately correlated with symptom change scores on all outcome measures. To further understand the participants’ experience with TAICBT, ten open-ended questions will be asked.

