***Method****.* Using a randomized controlled design, 58 women will be randomized to receive either TAICBT treatment or assigned to a 7-10 week WLC. Participants assigned to the WLC will receive a pamphlet that includes information on information on PPD and websites for support services offered in Saskatchewan. The intervention will consist of a seven-module TAICBT program adapted for women afflicted with PPD. Each TAICBT participant will be assigned to a therapist who they can correspond with weekly via email. Potential participants will be screened using the **Edinburgh Postnatal Depression Scale** (EPDS; Cox et al., 1987), modules from the **MINI International Neuropsychiatric Interview** (Sheehan et al., 1998), as well as standard screening questions. If deemed eligible, the following additional outcome measures will be administered: (a)**Depression Anxiety Stress Scale- Short Form** (DASS; Lovibond & Lovibond, 1995) to measure levels of depression, stress, and anxiety; (b)**Parenting Stress Index- Short Form** (PSI-SF; Abidin, 1995) to assess stress in the parent-child system; (c) **World Health Organization Quality of Life – BREF** (WHOQOL-BREF; WHOQOL Group, 1998) to assess quality of life;(d) **Therapist Alliance Questionnaire** (TAQ; Kiropoulos et al., 2008, modified from Luborsky’s 1985 HAQ-II) to determine the degree to which participants perceive the relationship with their therapist as helpful; (e) **Treatment Satisfaction Questionnaire-Modified** (TSQ; Cox et al., 1994) to assess the client’s perceived satisfaction with treatment; and (f) **Credibility/Expectancy Questionnaire**(CEQ; Devilly & Borkovec, 2000) to measure credibility and treatment expectancy of the TAICBT treatment. The TAQ, TSQ, and CEQ will only be completed by those participants receiving TAICBT treatment. All other measures will be completed by both groups of participants at pre-treatment and post-treatment (10 weeks after baseline). Following the 7-10 week wait, participants in the WLC group will be contacted, re-screened, and if still eligible, they will be offered the treatment. At this time, the TAICBT participants will be asked to respond to ten open-ended questions regarding their experiences with the program. To provide a longer-term follow-up of depressive symptoms, TAICBT participants will be contacted by telephone four weeks following treatment completion and administered the EPDS and the depression module of the MINI.

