# Section III: Subjects

1. **Briefly describe the number and characteristics of participants required for the study, and how a potential sample of such participants will be identified.**

Participants will include approximately 58 women residing in Saskatchewan seeking TAICBT treatment for symptoms of PPD. Potential participants will respond to advertising for *Maternal Depression Online* or will be referred by healthcare providers. Next, participants will be screened through questions on the Online Therapy USER website and by telephone to determine if they are eligible for TAICBT services and whether this form of service is appropriate for their concerns.

A woman will be deemed eligible to participate if she is a Saskatchewan resident, 18 years or older, meets diagnostic criteria for major depression or sub-clinical depression, and has a child under 12 months of age. Diagnostic criteria for PPD and sub-clinical PPD will be determined using cut-off scores on the Edinburgh Postnatal Depression Scale (Cox et al., 1987; see Appendix C) and a structured clinical interview for psychological disorders (MINI; Sheehan et al., 1998; See Appendix E).Participants will also be required to have regular access to a computer and the internet and endorse familiarity and comfort with using them. Lastly, participants will need to provide a contact name and number of a physician or another medical contact as this contact will be notified of the client’s participation in the online treatment program (see Appendix N).

Participants will be excluded from the study if they do not meet the above criteria or if they are (a) currently receiving psychotherapeutic treatment elsewhere or in some other form; (b) meet criteria for current substance abuse or dependence (drugs or alcohol); (c) meet criteria for a current psychotic disorder or bipolar disorder, or severe symptoms of depression, including suicidal ideation; or (d) report having a serious medical condition that may interfere with treatment completion.

2. Describe the recruitment procedures. Who will approach potential participants (researcher, assistant or third party) and how (e.g. by phone, mail)?

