APPENDIX I. PARENTAL STRESS INDEX-SHORT FORM (PSI-SF)^[[4]](#footnote-4)^

**APPENDIX C. PARENTAL STRESS INDEX-SHORT FORM^[[5]](#footnote-5)^**

Instructions: This questionnaire contains 36 statements. Read each statement carefully. For each statement, please focus on the child you are most concerned about, and circle the response that best represents your opinion.

Select SA if you strongly agree with the statement.

Select A if you agree with the statement.

Select NS if you are not sure.

Select D if you disagree with the statement.

Select SD is you strongly disagree with the statement.

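### As printed in Appendix I, the PSI-SF repeats one sentence as items 35 and 36, so it holds 35 distinct statements, not 36

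*Protocol*

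**What the plan says.** The protocol's Purpose and Hypotheses section names parental stress among the efficacy outcomes: the treatment is to be tested for "reducing depressive symptom severity, anxiety, general stress, parental stress, and for improving quality of life for women with PPD". The Method section assigns the PSI-SF to this outcome, "to assess stress in the parent-child system", and has both groups complete it before and after treatment.

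Appendix I reproduces the form. Its instructions state "This questionnaire contains 36 statements", and the rows are numbered 1 to 36. The last two are "35. My child makes more demands on me than most children" and "36. My child makes more demands on me than most children".

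The same instructions say which child to rate: "please focus on the child you are most concerned about". Eligibility (Section III, question 1) requires that the woman "has a child under 12 months of age" and does not exclude women with older children. Appendix D asks for the number and ages of all her children.

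**The concern.** A form that announces 36 statements and prints one of them twice has lost an item. If it is used as printed, the parenting-stress total gives one statement double weight and leaves another out. Missing item content cannot be recovered at the analysis stage, so this is not something a later analysis plan could put right. The total would also stop being the instrument's own score, and reading it against published values would no longer be sound.

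A smaller matter is that the instruction leaves the choice of child to the mother at each survey. A mother of several children could rate one child at baseline and another after treatment. Her change score would then partly reflect the switch.

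**Working it through.** **Inputs.** The stated number of statements and the item wordings come from Appendix I. The outcome role and timing come from the Purpose and Hypotheses and Method sections. The protocol gives no scoring rule, so steps 2, 3 and 5 assume an unweighted sum. Steps 3 and 5 also assume 1 to 5 points per item.

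**1. Count.** The stated figure of 36 is reproduced by the numbering: there are 36 rows. Comparing the wordings finds exactly one matching pair, items 35 and 36. Distinct statements = 36 − 1 = 35. The two rows carry separate numbers and separate response columns, so a fault in reading the PDF is unlikely.

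**2. Weight.**
- Intended: 1/36 = 2.8% of the total per statement.
- As printed, for the repeated statement: 2/36 = 5.6%.

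**3. Points.**
- The total runs from 36 × 1 = 36 to 36 × 5 = 180, a span of 144.
- The repeated statement accounts for 2 × 4 = 8 of those points instead of 4.
- For one woman at one survey, printed total − intended total = (answer on the surplus row) − (answer she would have given to the missing item).
- That difference lies between 1 − 5 = −4 and 5 − 1 = +4, so it is at most 4/144 = 2.8% of the span.

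**4. Effect on the group comparison.** Both arms would receive the same form at both times. The treatment effect on the printed total equals the effect on the intended total plus (effect on the repeated statement − effect on the missing item). If treatment changes no item, that extra term is zero in expectation, so the duplicate does not create a spurious difference. If treatment works, the estimate refers to a slightly different composite.

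**5. Recovery if data already exist.** Counting the repeated statement once gives a 35-item sum from 35 to 175. Multiplying by 36/35 returns it to 36 to 180.

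**6. How much of the scale depends on the rated child.** Items 13 to 21 (9 rows) and 23 to 36 (14 rows) refer to the respondent's own child: 9 + 14 = 23. Items 2, 4, 5 and 8 also mention a child or children: 23 + 4 = 27 of 36 rows. The documents do not give the share of women with more than one child or the frequency of switching, so no size can be put on this part.

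**The case against.** **The appendix may not be the administered form.** Participants answer on an online survey platform whose screens are not in the documents, and the appendix's footnote 5 points to the publisher's product. Appendix I looks retyped: it carries a stray second heading as Appendix C and several typing slips. A reader might infer that an item has been lost for all 58 women at both surveys. The documents do not show that. They show a printed error that may or may not have been carried online. This objection stands, and the point is conditional on it.

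**The effect is small and falls on both arms alike.** This also stands. The harm is to content and comparability, not to the randomised contrast.

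**Clinical-significance cut-offs.** A reader might infer that the Jacobson-Truax classification is undermined because published PSI-SF norms feed it. The Analysis section names the method. It does not say that it will be applied to the PSI-SF or that published norms will be used instead of the trial's own data, so that inference is not supported.

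**Subscales.** A larger weight could be obtained by assuming that the form splits into equal subscales. No subscale structure appears in the protocol, so no such figure is used here.

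**The rated child.** A reader might infer that the mother may pick any child, or that the form must be tied to the infant. Neither follows. The instruction is a selection rule, the child of most concern, and may be the instrument's own wording. The outcome is framed as parental stress, not stress about the infant. Rewriting the instruction would itself depart from the instrument. What remains is that nothing keeps the rated child the same across the two surveys, which affects only mothers of more than one child. There is no reason given to expect switching to differ by arm.

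**Conclusion.** The printed form is in error: it promises 36 statements and contains 35. That much is certain from the page. Which item is missing cannot be told from the documents.

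The consequence for the data rests on two assumptions: that the online survey carries the same text, and that the items are summed unweighted. Under both, one statement carries twice its intended share and one item goes unasked, so the total is not the instrument's score and should not be set against published values. Bias in the comparison of treatment with waitlist is not expected. This is an inexpensive correction to one of several outcomes and does not threaten the trial's main conclusion.

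The unfixed child is a secondary, low-priority matter of possible noise in the change score, of unknown size.

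**What to change.** Before data collection, proof all 36 lines of Appendix I and of the online form against the licensed PSI-SF, and replace the duplicated line with the item that is missing. The wording must come from the licensed form. The cost is a short proofread and a one-line correction.

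If data have already been collected on the duplicated form, count the repeated statement once, using a rule fixed in advance for women who answered the two rows differently (for example, the mean of the two answers). Prorate by 36/35 if a summed total is used, and report the departure from the instrument.

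As a low-priority addition, record at baseline which child is being rated. In the survey preamble, ask that the same child be rated after treatment, and leave the instrument's own wording unchanged. This costs one extra question and one sentence.

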**WHOQOL-BREF**

The following questions ask how you feel about your quality of life, health, or other areas of your life. I will read out each question to you, along with the response options. **Please choose the answer that appears most appropriate.** If you are unsure about which response to give to a question, the first response you think of is often the best one.

Please keep in mind your standards, hopes, pleasures and concerns. We ask that you think about your life **in the last four weeks.**

|  |  | Very poor | Poor | Neither poor nor good | Good | Very good |
| --- | --- | --- | --- | --- | --- | --- |
| 1. | How would you rate your quality of life? | 1 | 2 | 3 | 4 | 5 |

|  |  | Very dissatisfied | Dissatisfied | Neither satisfied nor dissatisfied | Satisfied | Very satisfied |
| --- | --- | --- | --- | --- | --- | --- |
| 2. | How satisfied are you with your health? | 1 | 2 | 3 | 4 | 5 |

The following questions ask about **how much** you have experienced certain things in the last four weeks.

|  |  | | Not at all | | A little | | | A moderate amount | | Very much | An extreme amount | |  |
| --- | --- | --- | --- | --- | --- | --- | --- | --- | --- | --- | --- | --- | --- |
| 3. | To what extent do you feel that physical pain prevents you from doing what you need to do? | | 5 | | 4 | | | 3 | | 2 | 1 | |  |
| 4. | How much do you need any medical treatment to function in your daily life? | | 5 | | 4 | | | 3 | | 2 | 1 | |  |
| 5. | How much do you enjoy life? | | 1 | | 2 | | | 3 | | 4 | 5 | |  |
| 6. | To what extent do you feel your life to be meaningful? | | 1 | | 2 | | | 3 | | 4 | 5 | |  |
|  | |  | | Not at all | | A little | A moderate amount | | Very much | | | Extremely | |
| 7. | | How well are you able to concentrate? | | 1 | | 2 | 3 | | 4 | | | 5 | |
| 8. | | How safe do you feel in your daily life? | | 1 | | 2 | 3 | | 4 | | | 5 | |
| 9. | | How healthy is your physical environment? | | 1 | | 2 | 3 | | 4 | | | 5 | |

The following questions ask about how completely you experience or were able to do certain things in the **last four weeks**.

|  |  | Not at all | A little | Moderately | Mostly | Completely |
| --- | --- | --- | --- | --- | --- | --- |
| 10. | Do you have enough energy for everyday life? | 1 | 2 | 3 | 4 | 5 |
| 11. | Are you able to accept your bodily appearance? | 1 | 2 | 3 | 4 | 5 |
| 12. | Have you enough money to meet your needs? | 1 | 2 | 3 | 4 | 5 |
| 13. | How available to you is the information that you need in your day-to-day life? | 1 | 2 | 3 | 4 | 5 |
| 14. | To what extent do you have the opportunity for leisure activities? | 1 | 2 | 3 | 4 | 5 |

|  |  | Very poor | Poor | Neither poor nor good | Good | Very good |
| --- | --- | --- | --- | --- | --- | --- |
| 15. | How well are you able to get around? | 1 | 2 | 3 | 4 | 5 |

|  |  | Very dissatisfied | Dissatisfied | Neither satisfied nor dissatisfied | Satisfied | Very satisfied |
| --- | --- | --- | --- | --- | --- | --- |
| 16. | How satisfied are you with your sleep? | 1 | 2 | 3 | 4 | 5 |
| 17. | How satisfied are you with your ability to perform your daily living activities? | 1 | 2 | 3 | 4 | 5 |
| 18. | How satisfied are you with your capacity for work? | 1 | 2 | 3 | 4 | 5 |
| 19. | How satisfied are you with yourself? | 1 | 2 | 3 | 4 | 5 |
| 20. | How satisfied are you with your personal relationships? | 1 | 2 | 3 | 4 | 5 |
| 21. | How satisfied are you with your sex life? | 1 | 2 | 3 | 4 | 5 |
| 22. | How satisfied are you with the support you get from your friends? | 1 | 2 | 3 | 4 | 5 |
| 23. | How satisfied are you with the conditions of your living place? | 1 | 2 | 3 | 4 | 5 |
| 24. | How satisfied are you with your access to health services? | 1 | 2 | 3 | 4 | 5 |
| 25. | How satisfied are you with your transport? | 1 | 2 | 3 | 4 | 5 |

The following question refers to how often you have felt or experienced certain things in the last four weeks.

|  |  | Never | Seldom | Quite often | Very often | Always |
| --- | --- | --- | --- | --- | --- | --- |
| 26. | How often do you have negative feelings such as blue mood, despair, anxiety, depression? | 5 | 4 | 3 | 2 | 1 |

APPENDIX K. THE THERAPEUTIC ALLIANCE QUESTIONNAIRE (TAQ)^[[7]](#footnote-7)^

There are ways that a person may feel or react in relation to another person. Consider carefully your relationship with your therapist, and then place a score in the rating column (based on the scale below), according to how strongly you agree or disagree. Please score every one.

| Strongly disagree | Disagree | Slightly Disagree | Slightly Agree | Agree | Strongly Agree |
| --- | --- | --- | --- | --- | --- |
| 1 | 2 | 3 | 4 | 5 | 6 |

|  | *Question* | Rating (0-6) |
| --- | --- | --- |
| 1 | I found I was able to rely on my therapist. | _______ |
| 2 | I felt my therapist understood those concerns that were important to me. | _______ |
| 3 | I felt my therapist was helping me to achieve my goals. | _______ |
| 4 | My therapist and I worked well together throughout the treatment program. | _______ |
| 5 | I believe that my therapist and I viewed my concerns in a similar way. | _______ |
| 6 | I felt comfortable with my therapist’s ability to guide me through the program. | _______ |
| 7 | I believe that the techniques used in the program were beneficial. | _______ |
| 8 | I developed a respect for my therapist. | _______ |
| 9 | I felt that my therapist and I were able to communicate effectively. | _______ |
| 10 | Our communications seemed to slow my treatment progress. | _______ |
| 11 | I regarded my therapist’s view about me. | _______ |
| 12 | I felt that I developed a good relationship with my therapist. | _______ |
| 13 | My therapist appeared to be competent in helping people. | _______ |
| 14 | I had meaningful communications with my therapist. | _______ |
| 15 | At times, I had fruitless exchanges with my therapist. | _______ |
| 16 | I believed the therapist respected me. | _______ |
| 17 | At times, I felt that my therapist appeared distant. | _______ |

